## Abstract

**Background:**

Musculoskeletal disorders (MSD) are common among dental professionals. The most common areas affected are the trunk, neck, shoulders and wrists. Current evidence suggests that the causes of MSD can be found in the physical demands of the profession. Posture and movement during treatment is influenced by the arrangement of the treatment concept (patient chair, equipment and cabinets). It has not been investigated whether the ergonomic risk differs between the treatment concepts.

**Methods:**

To evaluate the prevalence of MSD in dental professionals, 1000 responses will be collected from a nationwide (Germany) online questionnaire (mod. Nordic Questionnaire and mod. Meyer questionnaire). In order to assess the ergonomic risk of the treatment techniques used in the four treatment concepts, 3D movement analyses are carried out with inertial sensors. For this purpose, 20 teams of dentists and dental assistants from four dental fields of specializations (generalists, orthodontists, endodontists and oral surgeons) and a student control group will be recruited. Each team will execute field specific standardized treatments at a dummy head. Measurements are carried out in each of the four treatment concepts. The data will be analyzed using the Rapid Upper Limb Assessment (RULA) which will be modified for the evaluation of objective data.

**Conclusions:**

On the basis of these investigations, a substantial gain of knowledge regarding work-related MSD in the field of dentistry and its potential biomechanical causes is possible. For the first time, objective and differentiated comparisons between the four treatment concepts are possible for different fields of dental specialization. Up to now, statically held positions of the trunk and proximal upper extremities, but also the repetitive movements of the hands have been considered a risk for MSD. Since both are included in the RULA, dental activities can be assessed in a detailed but also global manner with regard to ergonomic risks.

## Background

Musculoskeletal disorders (MSD) are common among dental professionals [1–6]. The prevalence of MSD among dentists, dental assistants and dental students varies between 10.8 and 97.9% dependent on the body region according to Lietz et al. [2]. The trunk, neck, shoulders and wrists are the most commonly affected areas [1, 2, 4, 7, 8], often resulting in sick leave or even premature retirement [6, 8–11]. According to Brown et al. [9] a questionnaire survey of early retired dentists from a British insurance company found that MSD are the main cause of ill health retirement at 55%.

In general, the study situation indicates that the causes of MSD are related to the physical demands of the dental profession [3, 12]. The complex and fine-motor activities in the patient’s mouth, which is difficult to inspect, often require the sole attention of the practitioner. Ergonomic posture is therefore neglected in favor of better vision, although initial studies show that an upright trunk posture does not necessarily reduce the quality of treatment [13]. Posture is often static in awkward postures, especially in the trunk, neck and head, while treatment techniques require many, short and repetitive movements of the arms and hands [1, 3].

In addition to the narrow patient’s mouth, the arrangement of the dental workplace (patient chair, equipment and cabinets) also influences the posture and movement of the dental professionals. In the arrangement of the components, a distinction is made between four different treatment concepts [14–16] (Fig. 1). In all four concepts it is planned that the dentist performs treatment together with an assistant. Accordingly, both must have (ergonomically) appropriate access to the necessary equipment and materials and be able to inspect and to work in the patient’s mouth. Although MSD have already been the subject of much research in dentistry, a distinction between the various basic concepts and between the various specializations has not yet been considered.

**Fig. 1 Fig1:**
[figure not shown]
Treatment concepts 1–4 after Kimmel [17]

Current knowledge on MSD in dentistry is mainly derived from questionnaire surveys [1, 5, 6, 8, 18, 19] and from EMG studies [3, 20–22]. In the area of questionnaire surveys on work-related MSD, various approaches have already been carried out [18, 23, 24]. An established tool is the Nordic Questionnaire [25], which has already been used for the survey of musculoskeletal complaints in dentistry [8, 19, 26]. In EMG studies, high average strains were found for the trapezius muscle [20, 22], the splenius capitis muscle [3, 21] and the extensor carpi radialis [22] independent of the treatment performed.

However, objective data from movement analyses on actual posture in dentistry are only available to a limited extent for dentists [12, 27–30], but not for working with assistants. For example Ohlendorf et al. [29, 30], identified static (> 4 s) awkward postures in generalists and orthodontists. These are characterized by flexion and unilateral rotations in the head and trunk area and therefore simulate the typical dental treatment positions. In addition, the same working group was able to show with a combination of task and movement analysis that awkward postures are more likely to occur during dental treatment (generalists: 41% of the working day; orthodontists: 28% of the working day) than during computer work [12, 27]. The subjects worked predominantly in a seated posture (treatment and computer work). The direct comparison of the activities of generalists and orthodontists showed that dentists showed more unfavorable postures [28].

Basically, in the dental fields of specializations there is general dentistry and orthodontics as well as endodontology and oral surgery. It would be possible that the different treatments could influence the posture [3, 7, 12, 27–30]. It is also unclear whether these movement patterns only become established with increasing years of work, or whether students and trainees already acquire unfavorable movement patterns [31]. Overall, there is insufficient information about MSD and the potential influencing factors in dental professions to recommend appropriate preventive measures for dentists and their assistants.

The Rapid Upper Limb Assessment (RULA) [32, 33] is frequently used internationally to assess the ergonomic risk of workflow processes. The focus is on the body regions neck, shoulders, trunk, arms and hands with a predominantly kinematic approach. Although RULA was originally developed for observational assessment, there are already approaches to apply the tool to data from movement analyses collected with inertial sensors [34–36].

Various approaches are available to adequately respond to any possible ergonomic hazards. While changes in the arrangement of the equipment in the four treatment concepts can be assigned to the area of relational prevention, there are already behavioral prevention approaches. For example, ergonomic training courses on posture and treatment techniques are offered commercially. However, their effectiveness has hardly been scientifically investigated to date. Besides the education of ergonomic working methods, strength training can also be a promising approach to behavioral prevention in dentistry. Strength training is intended to strengthen the trunk muscles so that awkward postures can also be compensated more effectively [37]. Similar to ergonomic training, there are no studies to date on the effectiveness of such strength training specifically for dentists.

### Aims

The aim of this study is to comprehensively investigate MSD in the dental professional field. Initially, a Germany-wide online questionnaire will be used to collect data on MSD, work flow and health-related activities among dental professionals. Furthermore, an ergonomic risk assessment of the cooperative treatment of dentists and dental assistants based on objective movement data will be carried out for the first time. This will be done for four specializations (generalists, oral surgeons, endodontists and orthodontists) and a control group of dental students and dental assistant trainees at each of the four treatment concepts. The activities will be carried out in a standardized manner on the dummy head, so that differences between the treatment concepts can be recognized.

## Methods

### Subjects

#### Online survey

For the Germany-wide online survey, a total of at least 1000 completed questionnaires are targeted in the return. The target group includes dentists and dental assistants as well as dental students and dental assistant trainees.

#### Biomechanical analysis

For the biomechanical measurements, the aim is to recruit 20 teams of dentists and dental assistants in each of the four fields of dental specialization (generalists, endodontists, oral surgeons and orthodontists) and also in the control group (students/trainees). Both women and men between the ages of 18–65 years who treat right-handed are included.

Exclusion criteria include current injuries to the musculoskeletal system (e.g. herniated discs, spinal injuries), rheumatic diseases, severely restrictive malformations (scoliosis) of the spine or stiffened spinal joints (pathological or surgical), genetically determined muscular diseases and surgery less than 2 years ago. In the control group, dental students and trainees as dental assistants with treatment experience are included.

The study is approved by the Ethics committee of the Department of Medicine of the Goethe University Frankfurt am Main (356/17).

### Recruitment

The distribution of the questionnaire link as well as the search for participants for the biomechanical measurements will be carried out via the different German dental associations. In order to reach the highest possible number of practicing dentists and dental assistants for the questionnaire, the acquisition of study participants will be done through the state dental associations of all German federal states. In addition, a flyer for the survey is to be created, which will be distributed at various dental meetings. In order to include a high number of dental students, all medical university clinics in Germany will be contacted.

### Measurement protocol

#### Online survey

The online questionnaire is composed and supplemented from the Nordic Questionnaire by Kuorinka et al. [25] and from the questionnaire according to Meyer [18] on the workload of dentists working in a private practice.

Questions from the Nordic Questionnaire [25] on the prevalence of MSD in the regions of neck, upper and lower back, shoulders, elbows and wrists/hands as well as hips/thighs, knees and ankles/feet are included in the questionnaire. This is done for lifetime prevalence, 12-month prevalence, 3-month prevalence and 7-day prevalence. From Meyer’s questionnaire [18] questions on work restrictions, personal/psychological occupational stress and activities of daily living (ADLs) are included. Questions on health-related activities are also included, for example, whether the person has already participated in an ergonomics training course. In addition, working habits and spatial conditions of daily work as well as previous illnesses of the musculoskeletal system are also examined. Sociodemographic data and medication intake are also included.

The questionnaire will be created online via the SoSci Survey server. A pretest will be carried out to check the practicability and quality of the questionnaire. In the pretest, in addition to the regular answering of the questionnaire, comments on the individual pages should be possible in order to note remarks and difficulties in understanding. Based on the pretest the questionnaire will be adapted if necessary. The questionnaire is used in this study both in the Germany-wide survey and prior to the biomechanical analysis.

#### Motion capturing

The recording of the posture in the different test situations will be carried out by means of the inertial motion capture system MVN Link from XSens (Enschede, Netherlands). Sampling rate is 240 Hz and the measurement error is specified by the manufacturer as ±1%. By means of 17 sensors 22 joints will be interpolated.

After the measuring suit has been put on, the recordings take place over a period of 1 h on each of the four treatment concepts (4 h in total): On a dummy head, which is attached to each of the four treatment concepts, dental activities per specialization are carried in a standardized sequence (Fig. 2). The activities within each specialization are performed in all four quadrants (Table 1 for treatments of the respective fields of dental specialization). In addition to the individual biomechanical analysis, the interaction between dentist and dental assistant is recorded synchronously. In order to be able to allocate the activities exactly, the entire measurement sequence is filmed simultaneously in a total view (iPad Air, Apple Inc., Cupertino, California, United States; resolution: 1080p HD, 120fps). Therefore, measurement system and the camera will be synchronized by means of the software. Due to the character of the work, no randomization of the tasks will be carried out.

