### Limitations

The questionnaires will be distributed through a non-probabilistic procedure and the people contacted can decide to participate self-selectively. Therefore, a distortion is possible, as especially persons who are interested in ergonomic topics in dentistry could be motivated to participate. The representativeness of the results could be affected.

Since the measurements are carried out in laboratory settings, it is possible that no realistic measurement conditions are available. The recordings are not made in the dentists own practice, so that routine work processes may not be correctly recorded. In addition, a dummy head is used to improve the standardization of work processes. The movement frame of the dummy head is based on physiological conditions. The risk of setting unrealistic head positions on the dummy is therefore low. However, under real conditions, it should be noted that the mobility of the cervical spine varies in patients.

No conclusions can be drawn on the dose-response relationship between posture and MSD on the basis of this study. If, however, it is known which basic concepts and working methods are fundamentally in favor of unergonomic working methods, follow-up studies in this field can specifically determine the duration and frequency of treatments in practice.

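### Concept differences are read as effects of the arrangement, but teams may know one concept better than the others, and the stated presentation cannot show this

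*Protocol article*

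**What the plan says.** All references are to the protocol article.

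- **Aims** states the inference: "The activities will be carried out in a standardized manner on the dummy head, so that differences between the treatment concepts can be recognized". The Discussion repeats that standardised tasks on a dummy head make the concepts comparable, and says that any differences can feed into preventive measures.
- **Motion capturing** gives the session: "After the measuring suit has been put on, the recordings take place over a period of 1 h on each of the four treatment concepts". Together the recordings take 4 h.
- **Subjects, Biomechanical analysis** sets the numbers: "the aim is to recruit 20 teams of dentists and dental assistants in each of the four fields of dental specialization", and likewise in the control group. On that group it adds: "In the control group, dental students and trainees as dental assistants with treatment experience are included".
- **Recruitment** says that the "search for participants for the biomechanical measurements will be carried out via the different German dental associations". The habitual concept is not a recruitment or eligibility criterion.
- **Measurement protocol, Online survey** lists "working habits and spatial conditions of daily work" among the topics, and adds: "The questionnaire is used in this study both in the Germany-wide survey and prior to the biomechanical analysis".
- **Statistical data analysis** presents RULA scores for dentists and assistants separately, by concept and by field. It does not mention the habitual workplace.
- **Limitations** concedes: "The recordings are not made in the dentists own practice, so that routine work processes may not be correctly recorded".

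**The concern.** Standardising the task and the head makes the work the same on every concept. It does not make the team's experience of the layout the same. Crossing teams over all four concepts cancels whatever is constant within a team, such as build, skill or general working style. Familiarity with a layout is not constant within a team: it may be high on one concept and low on the rest.

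The study's own reasoning makes habit a plausible influence on posture. The Background asks whether movement patterns become established over years of work, and the Discussion expects the comparison with students to help answer that.

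If many of the recruited teams share one habitual concept, its score mixes the effect of the arrangement with the effect of being used to it. The mix could differ between fields, and between dentist and assistant. A preventive recommendation for or against a layout could then rest partly on who was recruited. This is separate from the order in which the concepts are recorded: balancing the order would not remove it.

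**Working it through.** **No figure to reproduce.** The article gives no effect size, SD or power for the biomechanical part. The check is algebra with assumed inputs.

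**Model.** For team i on concept c, let score = a_i + m_c + f × [c is the team's own concept].
- a_i is the team's general level.
- m_c is the effect of the arrangement.
- f is the score change from working on one's own concept. It is negative if familiarity lowers the risk score and positive if it goes with entrenched awkward posture.

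**Mean contrast over all teams.** mean(k) − mean(j) = (m_k − m_j) + f × (p_k − p_j), where p is the share of teams used to a concept. The a_i cancel because every team is on both concepts. The last term stays, and more teams do not shrink it.

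**Inputs.** From the article: 20 teams per group. Assumed: the split of habitual concepts, and f in RULA points. The table gives the size of the shift between the most and the least common concept.

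| Assumed split of 20 teams | p_k − p_j | size of f = 0.25 | 0.5 | 1.0 |
|---|---|---|---|---|
| 5/5/5/5 | 0.25 − 0.25 = 0 | 0 | 0 | 0 |
| 10/4/4/2 | 0.50 − 0.10 = 0.40 | 0.10 | 0.20 | 0.40 |
| 16/2/1/1 | 0.80 − 0.05 = 0.75 | 0.19 | 0.38 | 0.75 |

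**Can the two effects be separated?** Take 16/2/1/1, compare concept 1 with concept 2, and write D = m_1 − m_2.
- The 16 teams used to concept 1 show D + f.
- The 2 teams used to concept 2 show D − f.
- The 2 teams used to neither show D.
- All teams together: [16(D + f) + 2(D − f) + 2D] / 20 = D + 14f/20 = D + 0.70f. This agrees with p_1 − p_2 = 0.80 − 0.10.

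The subgroups carry different multiples of f, so an own-concept indicator separates D from f, provided that habitual concepts vary between teams. If every team had the same habitual concept, the indicator would coincide with that concept and nothing could be separated. The distribution itself is therefore a necessary result.

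**Cell sizes.** In one field with this split, 20 − 16 − 2 = 2 teams are used to neither concept 1 nor concept 2. Over four specialist fields with the same split (80 teams: 64/8/4/4), it is 80 − 64 − 8 = 8. This is why the supplementary analysis should be pooled.

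**The case against.** The strongest reply is that much of this can be overstated, and on several points that is right.

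- **That teams come from practices working in one concept.** A reader might infer this. The article says only that dental workplaces are classed into four concepts and that participants are sought through associations. The inference is reasonable for practising teams but undocumented, and it fits the student and trainee group poorly.
- **That there is no familiarisation.** Recording follows once the suit is on, and no practice period is described. That is silence in a condensed article, and the full protocol may cover it. It is not a finding here.
- **That the habitual workplace is ignored.** Related information is collected before measurement, though the text does not say that the concept itself is recorded. A split could also be planned in a document not shown. What stands is that the article draws its inference about arrangement from a stated presentation that omits this information.
- **That the commonest concept will look better.** The sign is unknown. The article's own question about unfavourable patterns becoming established makes the opposite direction possible.
- **That comparing only unfamiliar concepts would be like for like.** It would not. With 16/2/1/1, concept 1 would rest on 20 − 16 = 4 teams and concept 2 on 20 − 2 = 18, with only 2 in common. That gives up the within-team comparison.

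The existing limitation about not working in one's own practice concerns realism in all four conditions. It does not cover unequal familiarity between them. The objection leaves that gap untouched.

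**Conclusion.** The point stands as a possible bias that the stated presentation cannot detect. It is neither a contradiction nor a demonstrated error. Standardised tasks and the crossed design do not by themselves justify reading concept differences as pure effects of the arrangement.

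The shift in a contrast is f × (p_k − p_j). It is zero if habitual concepts are evenly spread or if familiarity has no effect. Under the assumed uneven splits, with f between 0.25 and 1.0 points in size, it is about 0.1 to 0.75 RULA points between the most and the least common concept, in either direction. Both f and the splits are assumptions. The model also takes f as the same for every concept and team.

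The documents do not support the conclusion that the study is bound to favour a widespread layout. They do support collecting and using the habitual concept, because the questionnaire that could supply it is already part of the session.

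**What to change.** 1. **Questionnaire.** Make sure that the version given before measurement identifies each participant's habitual concept, for example with the drawings in Fig. 1. Allow the answers none and several, and ask dentist and assistant separately.
2. **Main result.** Keep the within-team comparison of the four concepts in all teams.
3. **Supplementary result.** Add a within-team analysis by role with an own-concept indicator, pooled across fields. Alternatively, contrast each pair of concepts only in teams used to neither of the two. Both keep the within-team comparison.
4. **Reporting.** Give the distribution of habitual concepts by field and role, so that readers can judge how far p_k and p_j differ.
5. **Limitations.** Name unequal habituation between concepts, apart from the existing remark on the laboratory setting.

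**Cost.** One questionnaire item and a little more analysis; the recording session does not get longer. Cells will be small, so the supplementary result is descriptive. Pooling assumes that the own-concept effect is similar across fields. If nearly all teams share one habitual concept, the two effects cannot be separated well, and the report should say so.

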**Fig. 2 Fig2:**
[figure not shown]
Treatment of the phantom head when wearing the MVN Link system by Xsens. Subjects can move freely without interference with the measurement system

**Table 1 Tab1:** Standardized tasks for the fields of specialization: The group of general dentists and the control group of students execute the same tasks. All tasks in the four dental quadrants will be executed on each of the four treatment concepts

	Task	Quadrant 1	Quadrant 2	Quadrant 3	Quadrant 4
**General Dentistry/Students**		**Tooth filling of tooth 16**	**Preparation of tooth 26 for crown uptake**	**Root canal treatment on tooth 35**	**Tartar removal in the 4th quadrant**
	**1**	prepare tooth cavity with a cylindrical diamond bur and the use of wedges	Occlusal reduction using an occlusal reducer	Performing an entrance cavity and trepanation on tooth 35 using a diamond-coated cylinder	Removal of supra- and subgingival tartar/calculus using scalers an curettes
	**2**	Create a Tofflemire die using a die clamp	chamfer preparation using a torpedo-shaped diamond burand approximal reducer	Find the channel entrance using an endo file	
	**3**	Tooth filling with ketac® while using a ketac®-set and a cougar/heidemann		Manual preparation of the canal using an ISO 20-40 endo file with regular irrigation using a irrigation cannula	
**Endodontology**		**Root canal treatment of tooth 16**	**Root canal treatment of tooth 26**	**Root canal treatment of tooth 36**	**Root canal treatment of tooth 46**
	**1**	Application of the rubber dam	Application of the rubber dam	Application of the rubber dam	Application of the rubber dam
	**2**	Trepanation of the tooth and access preparation including the enlarging of the root canal entrance	Trepanation of the tooth and access preparation including the enlarging of the root canal entrance	Trepanation of the tooth and access preparation including the enlarging of the root canal entrance	Trepanation of the tooth and access preparation including the enlarging of the root canal entrance

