### Statistical data analysis

Only those questionnaires that have been fully completed will be included in the questionnaire evaluation. The data formatting is done via Excel. The questionnaires are checked for plausibility in the answering behavior. A category system will be developed for open answers. The questionnaire will be evaluated in IBM SPSS Statistics 26, and the questionnaire data will be evaluated descriptively, separately for dentists and dental students, and for dental assistants and trainees. Therefore, measures of location and dispersion corresponding to the scale level are calculated.

The data analysis of the biomechanical measurements is performed with MATLAB® vR2018a software (The Mathworks Inc., Natick, MA, USA). The RULA risk scores will be presented separately for dentists and dental assistants in each of the four treatment concepts for each field of dental specialization.

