A further advantage of the RULA is that both the statically held positions of the trunk and the proximal upper extremities are taken into account, as well as the repetitive movements of the hands, which also poses a risk for MSD [39, 41]. Questionnaire surveys in dental professionals have already shown in the past that wrists and hands are also affected by MSD [1, 39]. In addition to the movements, the vibration of the devices also contributes to this [42]. In Germany, only carpal tunnel syndrome is acknowledged as a musculoskeletal occupational disease in dentistry [43].

Although the body of literature is already relatively large with regard to ergonomic risk in dentists, a comparison of the different treatment concepts is still missing. Thus, it has not yet been considered whether the arrangement of the inventory and the positioning of dentist and assistant in relation to the patient have an influence on posture and movement sequences. If differences occur here, this information can be integrated into the development of preventive measures.

The aim should be that both practitioners complement each other in their grasping movements to the instruments and in their work in the patient’s mouth. This should reduce the physical strain on both. The presented study design with the standardization of the tasks performed on a dummy head allows comparisons between the treatment concepts for the first time.

Furthermore, the comparison of the specialization fields with the control group can be expected to contribute to the clarification of the question at which stage of the work experience unfavorable postures occur. Finsen et al. [3] for example, were able to show by means of a questionnaire survey that the prevalence of MSD increases with increasing years of work experience.

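### No randomised or counterbalanced order is specified for the four treatment concepts; if all teams share one order, concept cannot be separated from position in the session

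*Protocol article*

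**What the plan says.** All references are to the protocol article.

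- **Exposure (Motion capturing).** Once the suit is on, "the recordings take place over a period of 1 h on each of the four treatment concepts (4 h in total".
- **Task order (Motion capturing).** On each concept, "dental activities per specialization are carried in a standardized sequence", and the section ends: "Due to the character of the work, no randomization of the tasks will be carried out".
- **Repetition (Table 1 caption).** "All tasks in the four dental quadrants will be executed on each of the four treatment concepts". Every team therefore does the same work four times.
- **Team numbers (Subjects, Biomechanical analysis).** "the aim is to recruit 20 teams of dentists and dental assistants in each of the four fields of dental specialization", and the same number in the control group of students and trainees.
- **Purpose.** The Aims give standardisation on the dummy head as the means of recognising differences between concepts. The Discussion says the design with standardised tasks "allows comparisons between the treatment concepts for the first time".
- **Analysis (Statistical data analysis).** RULA scores are to be shown by role, concept and field. No order or period term is mentioned.
- **Limitations.** These cover self-selection, the laboratory setting and the dummy head. Order, fatigue and repetition are not among them.

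The order in which a team moves through the four concepts is not stated anywhere.

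**The concern.** The comparison of concepts within teams is the core of the biomechanical part. Its validity depends on whether the concept is the only thing that changes from one hour to the next. Over four hours of repeated work, position in the sequence changes as well: a team on its fourth concept has worked longer and has done the same procedures three times before.

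The article's stated safeguard is standardisation of the tasks. That makes the work the same on each concept, but does nothing about position. The usual safeguard is to vary the order of conditions between teams, and none is described. The reason given for not randomising, the character of the work, is a good one for steps within a treatment: etching precedes bonding and incision precedes suturing. It gives no reason why one concept should come before another.

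If the order is common to all teams, a time trend in posture cannot be told apart from a concept effect. The flaw would be built into the data and could not be repaired in the analysis.

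**Working it through.** The article gives no significance level, standard deviation, effect size or power, so there is no stated figure to reproduce. Its one sum, 4 x 1 h = 4 h, is consistent. The check is therefore structural, followed by an illustration.

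**1. Are concept and period separable?**

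Take one role in one group: 20 teams x 4 concepts = 80 scores. A model with team, concept and period has 20 + 3 + 3 = 26 parameters.

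- *One common order (assumed; the article does not state it).* The concept in position k is the same for every team, so the three concept columns equal the three period columns. Rank = 26 - 3 = 23. All three concept contrasts are aliased with period.
- *Williams square, 4 sequences x 5 teams.* Example sequences are 1-2-4-3, 2-3-1-4, 3-4-2-1 and 4-1-3-2. Rank = 26, so concept and period are separately estimable. Residual degrees of freedom are 80 - 26 = 54, against 80 - 23 = 57 without the period term.

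This result needs no assumption about the size of any drift.

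**2. What bias follows from a trend?**

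Let the score drift by d per hour, with positions 0, 1, 2 and 3.

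- *One common order.* The bias relative to the first concept is d, 2d and 3d.
- *Williams square.* Each concept stands five times in each position, so its mean position is (0 + 1 + 2 + 3)/4 = 1.5. Every concept has the same expected shift of 1.5d, and the bias in every contrast is 0. The same holds for any additive period effect, linear or not.

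**3. Illustration of size.**

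All inputs except n = 20 are assumptions: d = 0.05 to 0.15 RULA points per hour, standard deviation of within-person differences 0.4 to 0.6, and a 95% paired t interval for first versus last concept. The article plans no such interval. At SD 0.5, SE = 0.5/√20 = 0.112.

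| d per hour | Bias 3d | Bias/SE | Zero wrongly excluded, SD 0.5 | SD 0.4 | SD 0.6 |
|---|---|---|---|---|---|
| 0.05 | 0.15 | 1.34 | 25% | 36% | 19% |
| 0.10 | 0.30 | 2.68 | 72% | 89% | 56% |
| 0.15 | 0.45 | 4.02 | 97% | >99% | 89% |

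The percentages come from the non-central t distribution with 19 degrees of freedom; the nominal rate is 5%. The table shows only how sensitive the comparison would be. It is not evidence that a drift exists.

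**4. Does the fixed task order matter?**

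If the same sequence of tasks and quadrants is repeated on every concept, its effect is the same in all four concept means and cancels from their differences. A fixed task or quadrant order does not itself bias the concept comparison.

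**The case against.** The strongest objection is that the article never says the concept order is fixed. The sentence on randomisation is about tasks. Table 1 uses that word for the dental steps and keeps it apart from the concepts. A reader might infer that nothing at all is randomised, or that all teams follow one order. The text supports neither reading: it is silent on concept order, and a full protocol might settle it. This part of the objection stands, and it is why the point is conditional.

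Several other inferences also fail:

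- The Discussion does not claim that standardisation on its own makes the comparison valid. It credits the design with standardised tasks.
- Sensor calibration is not described, so drift since calibration cannot be argued from the text.
- Breaks between the hourly blocks are neither stated nor excluded, and a single continuous session is implied rather than stated.
- Faster learning in students is conjecture; the control group must already have treatment experience.
- The error rates above presuppose an interval that the article does not plan.

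It does not follow that the point is a mere reporting gap in a condensed article. The article takes up ordering, states a decision on it, and relies on task standardisation for the concept comparison without naming order effects as a limitation. Allocation of order is the basic safeguard of a within-team comparison, and its absence could not be made good after data collection.

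**Conclusion.** The concern holds in conditional form. The article rules out randomising the tasks and specifies no randomised or counterbalanced order for the concepts. If one order is used for all teams, aliasing of concept with position is complete: three of three contrasts, rank 23 of 26. Task standardisation does not remove it.

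This conclusion rests on one assumption, a common order, which the article neither states nor excludes. The size and direction of any resulting bias cannot be derived from the document. It would be three times the hourly drift for first versus last concept if the drift were linear. It would be wrong to read this as showing that the concept results will be biased, or that the fixed task sequence is a fault.

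**What to change.** Keep the task sequence fixed and add wording such as:

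*The sequence of tasks is the same on every treatment concept. The order of the four concepts is allocated to teams by a 4 x 4 Williams square, separately within each field and the control group (4 sequences x 5 teams = 20). Results by concept are summarised by, or adjusted for, period.*

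If the concept order is already varied, one sentence saying how is enough. If it cannot be varied, for example because of how the stations are set up, order effects should be listed under Limitations as a limit on the concept comparison.

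The cost is an allocation list and teams changing stations in different orders. If period is modelled, it uses 3 degrees of freedom. No extra teams or recording time are needed, because 20 divides evenly by 4. If a group falls short of 20 teams the balance becomes approximate, but concept and period remain separable as long as all four sequences are used.
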